### Data-handling

The data is securely stored in a folder with limited access by the involved researchers only and will be retained for 15 years after inclusion. To assure confidentiality, participant data (both paper-based and electronic data) is identified by a participant ID (see randomization and blinding). Electronic data is protected by a password. The file linking participant ID and personal information is stored in a separated file which is also password protected. To ensure data-quality, paper-based data entry will be double checked. Only the principal investigator and first author will have access to the final data-set. As the study involves low to negligible risk, no additional data monitoring committee is assigned. Results of this study will be published in national and international journals and will be presented at conferences. Moreover, participants and involved clinicians will receive a summary of the study results.

### Analyses

#### Sample size

Wells and Beevers [29] reported a large effect of ABM on change in bias (*η*
^*2*^ = .16) and on depressive symptoms (*η*
^*2*^ = .32). Likewise, Beevers et al. [35] observed a large effect for change in bias from pre- to post-ABM within the training condition (*d* = 1.01, *η*
^*2*^ = .20), but not the control condition (*d* = .04, *η*
^*2*^ = .0004). However, the above-mentioned studies were conducted in a sample of dysphoric students [29] and in a sample of treatment-seeking current MDD patients, some of whom received pharmacological treatment [35]. In the present study, ABM is provided during the waiting period for psychotherapy or in combination with pharmacological treatment and/or psychotherapy (i.e., IPT, CBT, psychiatric care). In order to account for the greater heterogeneity of our sample and because recent meta-analyses of the effects of CBM in anxiety and depression suggest rather small effects [28, 41], we conservatively assume a small to medium effect size of *η*
^*2*^ = .02 (i.e., *f* = .142). A-priori sample size is calculated with G*Power for F-tests for repeated-measures (RM) Analysis of Variance (ANOVA) with within-between interaction effects and an effect size specification as recommended by Cohen [83]. To be able to detect this effect size over two time-points, with an α-level of .05 and a power-level of .80, a total sample size of 100 would be needed, thus 50 participants per group. Compensating for an expected attrition of 20 %, we need to include 50/0.80 = 62.5, thus 63 participants per condition and *N* = 126 in total.

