### Aim and hypotheses

The present study aims to address above-mentioned limitations by means of an adequately powered, randomized, double-blind, placebo-controlled trial, alongside an economic evaluation, investigating the long-term effectiveness and cost-effectiveness of a dot-probe based ABM training, as self-help intervention for clinical depression in a specialized health care setting. One hundred twenty six patients who are diagnosed with MDD and are registered for specialized ambulatory treatment at the mental health care institute Pro Persona in the Netherlands, are randomized into either a positivity training (PT) group (ABM towards positive and away from negative stimuli) or a sham (i.e., placebo) training (ST) group, as control condition (continuous attentional bias assessment). Patients complete eight training sessions (of which seven at home via internet) during a period of two weeks. Changes in attentional bias are assessed from pre- to post-assessment, whereas effects on clinical symptoms are additionally assessed one, six and 12 months after training.

In line with previous research on ABM in depression, we predict that the PT group shows a stronger decrease in negative attentional bias and therefore a stronger decrease in depressive symptoms over time, than the ST group. As already suggested by findings of Wells and Beevers [29] and Beevers and colleagues [35], training effects on depressive symptoms are thus expected to be mediated by an decrease in negative attentional bias. Recent research by Yang and colleagues [32] however suggests, that the ABM effect on depressive symptoms is not directly mediated by change in bias. Instead, a change in bias appears to mediate a change in rumination, which in turn directly mediates the reduction of symptoms. Therefore, we additionally explore the effects of ABM on rumination and it’s mediating role in the effects of ABM on depression.

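### The 80% power claimed for η² = .02 with 100 completers holds only under an unstated specification and pre-post correlation; read plainly, power is about 29%

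*Protocol article*

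**What the plan says.** The Sample size section of the protocol article cites η² values of .16, .32 and .20 from two earlier studies, notes that meta-analyses suggest smaller effects, and says "we conservatively assume a small to medium effect size of" η² = .02, which it converts to f = .142. The method is described thus: "A-priori sample size is calculated with G*Power for F-tests for repeated-measures (RM) Analysis of Variance (ANOVA) with within-between interaction effects", with an "effect size specification as recommended by Cohen [83"]. The remaining inputs are "To be able to detect this effect size over two time-points" and "with an α-level of .05 and a power-level of .80". The result is that "a total sample size of 100 would be needed, thus 50 participants per group". Allowing for 20% attrition gives 63 per arm and 126 in total.

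The Clinical evaluation section confirms that attentional bias and depressive symptoms are to be tested by a 2 (condition) × 2 (pre, post) repeated-measures ANOVA. No correlation between the repeated measurements is given anywhere. Under Aim and hypotheses the study is called an "adequately powered, randomized, double-blind, placebo-controlled trial".

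**The concern.** With two arms and two time points, the interaction F-test is the same test as a two-sample t-test on pre-post change. An η² of .02 for that test is a small effect, and 50 patients per arm is far too few to detect it with 80% power. So either the power figure does not follow from the stated effect, or .02 measures something other than the interaction that will be tested.

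The article faults earlier studies for being small when the effects of this training are thought to be small, and presents this trial as the remedy. If the trial can reliably detect only a medium effect, a null result could be misread as evidence against the small-to-medium effect named in the plan.

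**Working it through.** **Inputs, all from the Sample size section:** η² = .02; f = .142 (exactly √(.02/.98) = .1429); two arms; two time points; α = .05; N = 100 analysed, 50 per arm. The pre-post correlation ρ is not given, so it is shown as a range. Power comes from the noncentral F distribution with 1 and N − 2 degrees of freedom.

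**1. Reproducing the plan's figure.** Take λ = f²·N·2/(1 − ρ) and assume ρ = .5.
- N = 100: λ = .142² × 100 × 2/.5 = 8.07, power .803.
- N = 98: power .795.

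The smallest balanced N is therefore exactly 100. The attrition step is also right: 50/0.80 = 62.5, rounded up to 63, giving 126.

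**2. The plain reading.** If .02 is the η² of the tested interaction, then λ = f²·N and no correlation enters.
- N = 100: λ = .142² × 100 = 2.02, power .290 (.293 with f = .1429).
- N = 126, all analysed: λ = 2.54, power .353 (.356 with f = .1429).
- 80% power: 392 completers with f = .142, 388 with f = .1429, so about 390.

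Check on change scores: the arms differ by d = 2f = 2 × .1429 = 0.286 SD of change. The noncentrality d²N/4 = .286² × 25 = 2.04 is the same quantity, and so is the power.

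**3. What N = 100 is really powered for.** The λ in step 1 is four times that in step 2 (8.07/2.02). Solving λ = f²·N for 80% power at N = 100 gives f = .283, hence partial η² = .0801/1.0801 = .074 and d = 2 × .283 = 0.57 SD of change.

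**4. Dependence on the unstated ρ, on the route of step 1 with f = .142:**

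| ρ | Power at N = 100 | N for 80% power |
|---|---|---|
| 0 | .51 | 198 |
| .2 | .60 | 158 |
| .3 | .66 | 140 |
| .5 | .80 | 100 |
| .6 | .88 | 80 |
| .7 | .95 | 62 |

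On this route f is scaled by the within-cell SD of the score. The difference in change is then 4f = 4 × .142 = 0.568 SD of the score, whatever ρ is. The SD of change is √(2(1 − ρ)) times the SD of the score, and the two are equal at ρ = .5. Check: .568² × 100/4 = 8.07, as in step 1.

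**The case against.** The strongest reply is that nothing was miscalculated. The section's reference to Cohen may mean only that the effect is expressed as Cohen's f, which the preceding sentence does. The text writes η², not partial η². If f = .142 is scaled by the within-cell SD, N = 100 follows exactly at ρ = .5, and a higher ρ would give more than 80% power. The article prints no noncentrality formula, and the source it cites for the specification is not at hand.

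Much of this stands. A reader might infer an arithmetic blunder, but the calculation is internally consistent on one recognised route. It does not rescue the paragraph, for two reasons. The 80% then rests on a correlation stated nowhere for either outcome. And .02 is then not the η² of the interaction being tested, although it is set beside η² values from earlier studies as if it were on the same footing.

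Three stronger readings are not supported:
- A reader might infer that the attentional bias score, being a reaction-time difference over 60 trials, has a low pre-post correlation and so still lower power. The document gives no correlation for it, and the range runs in both directions.
- A reader might infer that calling the assumption conservative is simply wrong. Even .074 is less than half of .16, the smallest of the large effects cited, so the word is fair as a comparison with those studies.
- A reader might infer that the number of patients must rise to about 390. The point concerns what is claimed for 126 patients; it does not show that the design must be enlarged.

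**Conclusion.** The point holds: the power statement is wrong as written. If .02 is the (partial) η² of the condition × time interaction, 100 completers give about 29% power, 126 would give about 35%, and 80% needs about 390. The stated N = 100 is recovered only with λ = f²·N·2/(1 − ρ) and ρ = .5, neither of which is disclosed. The effect then detectable with 80% power is about 0.57 SD of change, partial η² about .074, which is a medium effect.

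The 29% rests on taking η² as that of the tested interaction. The 80% rests on the alternative scaling and on ρ = .5. That this route was the one used is an inference from the exact match at N = 100; the article does not say so. On neither reading do the stated inputs alone support 80% power for a small-to-medium effect.

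**What to change.** Keep N = 126 and revise the Sample size paragraph:
- State which effect-size specification was used and the pre-post correlation assumed.
- Restate the result along these lines: *100 completers give 80% power for a between-arm difference in pre-post change of about 0.57 SD of change (partial η² about .074); power for partial η² = .02 is about 29%.*
- Describe the effect powered for as medium, not small to medium.
- Limit the word conservatively to the comparison with the larger effects cited from earlier studies.

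Under Aim and hypotheses, qualify the claim of adequate power by naming the effect size to which it applies.

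The cost is the rewording of one paragraph and one phrase elsewhere. Recruitment, outcomes and analysis do not change. The downside is that the stated power becomes less favourable.

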### Analysis plan

#### Clinical evaluation

In accordance with the Consolidated Standards of Reporting Trials (CONSORT; [84]), all analyses of the primary and secondary outcome parameters will be carried out in accordance with the intention-to-treat (ITT) principle. Missing values due to drop-out will be imputed (e.g., by using multiple imputation (MI) or expectation maximization (EM)). Additional sensitivity analyses will be conducted to gauge the robustness of the findings, by including and excluding these participants in the analysis.

ABM effects on the primary outcome measures, attentional bias and depressive symptoms, will be tested by means of RM ANOVAs, with condition (PT, ST) as between-subjects factor and time (pre-test, post-test) as within-subjects factor. Likewise, training effects on stress responses will be investigated with a 2 (condition: PT, ST) × 3 (time: before stress, anticipatory stress, stress recovery) RM ANOVA with I PANAS-SF and STAI-S scores as dependent variables. All analyses will be conducted with and without covariates, in case variables are unevenly distributed across groups (e.g., bias or depression at baseline, number of previous depressive episodes, or number of completed training sessions), to test the robustness of the results. To investigate long-term effects of ABM on depressive symptoms, the analysis of this primary outcome parameter will be repeated over five time points (baseline, post-test, one, six, and 12 months follow-up).

Effects on secondary outcome measures will be analyzed by means of ANOVAs or ANCOVAs over two time points (baseline, post-test) in case of the cognitive transfer measures, and over four time points (baseline, post-test, one and six months follow-up), in case of rumination, positive and negative affect, and resilience.

Exploratory analyses will be directed at the process measures and will additionally be performed to take the role of potential moderators into account, such as timing of the training (i.e., during waiting period vs. next to UC) type of UC (IPT, CBT, psychiatric care), or to predict training effects based on other disorder-related characteristics assessed during baseline.

Finally, mediation analysis will be conducted to investigate whether change in attentional bias across sessions mediates the relationship between training condition and depressive symptoms. A second exploratory mediation analysis will test the mediating effect of rumination. This analysis will only include participants who completed an adequate dose of training sessions (i.e., 6–8).

As alternative to general linear models (GLM), which have been the standard approach to analyzing data of similar trials as the one proposed, more recent statistical developments including linear mixed models (LMM) might be considered when analyzing the data.

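### EM fill-in is offered as an equal alternative to MI before the RM ANOVA; at the planned 20% attrition it either inflates the type I error to about .09-.11 or dilutes the effect by about a fifth

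*Protocol article*

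**What the plan says.** Under Clinical evaluation, the article commits to intention-to-treat and adds: "Missing values due to drop-out will be imputed (e.g., by using multiple imputation (MI) or expectation maximization (EM". Attentional bias and depressive symptoms are then tested by "RM ANOVAs, with condition (PT, ST) as between-subjects factor and time (pre-test, post-test) as within-subjects factor". For long-term effects on depressive symptoms, "the analysis of this primary outcome parameter will be repeated over five time points (baseline, post-test, one, six, and 12 months follow-up". The one stated check on missing data is a sensitivity analysis "by including and excluding these participants in the analysis". The last paragraph before the economic evaluation says that linear mixed models might be considered.

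The Sample size section gives the scale of the problem: "Compensating for an expected attrition of 20 %, we need to include 50/0.80 = 62.5, thus 63 participants per condition". About one participant in five may therefore need imputed outcomes.

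**The concern.** MI draws each missing value several times and combines the results, so that the uncertainty about the missing values reaches the standard error. EM as a fill-in method puts each missing value at its predicted mean and does so once. An ordinary RM ANOVA on that data set uses the full 126 participants and a residual variance that lacks the scatter of the missing values.

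Which fault follows depends on a choice that the article does not state:

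- **Condition in the EM model, or EM run by arm.** The effect estimate is unbiased but its standard error is too small, so the null is rejected too often.
- **Condition left out.** Drop-outs in both arms are placed on a common line, which pulls the arms together.

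A condensed article may leave imputation details to the analysis plan. Here, however, it names a specific method as acceptable ahead of the primary test, and that method gives a wrong standard error or a biased effect in either form.

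**Working it through.** **Inputs from the documents.** 63 per arm, 20% attrition, α = .05, two time points, condition × time test. With two time points this test equals a t-test on change scores (post minus pre).

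**Assumptions.** Outcomes are bivariate normal with SD 1. The 20% falls at post-test and is completely at random. The pre-post correlation ρ is not stated, so a range is shown.

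**Step 1: the plan's own figure.** "with an α-level of .05 and a power-level of .80, a total sample size of 100 would be needed, thus 50 participants per group". With f² = .02/.98 = .0204, m = 2 time points and ρ = .5, the noncentrality is λ = f²·N·m/(1−ρ) = .0204 × 100 × 2/.5 = 8.16. Power is .808 at N = 100 and just under .80 at N = 98, so N = 100 is reproduced. Dividing 50 by .80 gives 62.5, hence 63. I take ρ = .5 as the central value because it returns the stated N under this convention. A convention without the factor m/(1−ρ) gives 388, so ρ = .5 remains an inference. The corresponding difference in change is √8.163 × √(2/50) = .571.

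**Step 2: condition in the EM model, approximate formula.** With n per arm and missing fraction d:

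- Variance that the ANOVA assumes: (2/n)·[(1−ρ)² + (1−d)(1−ρ²)]
- True variance of the estimate: (2/n)·[(1−ρ)² + (1−ρ²)/(1−d)]

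At ρ = .5 and d = .2:

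- Assumed: (2/63)(.25 + .60) = .0270, SE = .164.
- True: (2/63)(.25 + .9375) = .0377, SE = .194.

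The SE is about 15% too small. The critical value 1.979 then acts as 1.979 × .846 = 1.674, and the two-sided rejection rate is about .094. At ρ = .2 the SE ratio is .875 and the rate .083; at ρ = .7 they are .827 and .102. The formula ignores small-sample error in the fitted line, so simulation gives slightly more.

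**Step 3: simulation under the null (6,000 to 8,000 runs per setting).**

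| Method, 20% missing | Type I error |
|---|---|
| EM with condition, ρ = .2 | .088 |
| EM with condition, ρ = .5 | .096-.100 |
| EM with condition, ρ = .7 | .098-.105 |
| EM by arm, ρ = .2 to .7 | .088-.105 |
| EM pooled, without condition | .047-.054 |
| MI, 20 imputations, Rubin's rules, condition included, ρ = .5 | .049 |
| Completers only, ρ = .5 | about .05 |

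Separate simulations over ρ = .2 to .7 with condition included spread from .088 to .112. At ρ = 0 the rate is .078. If drop-out depends on baseline (ρ = .5), it is .107. If only 10% are missing, it is .072.

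**Step 4: condition left out.** The imputed fifth carries no arm difference, so the expected estimate is .8 × .571 = .457. Simulation gives .455 to .457, a loss of 20%.

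**Step 5: power at the planning effect (ρ = .5).** MI .82, completers .81, pooled EM .78. EM with condition shows .90, but this comes with the inflated type I error and is not a real gain.

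**Step 6: five time points.** With drop-out accumulating to 20% and EM with condition or by arm, the type I error is .097 to .127 after Greenhouse-Geisser correction (2,000 runs per setting; compound symmetry with ρ = .5 or .7, and AR(1) with ρ = .7). Pooled EM with the same correction gives .047 to .054.

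**The case against.** The strongest reply has three parts.

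First, EM is not fixed. It is one of two examples, MI is named before it, and mixed models are mentioned as an alternative. This stands: the fault is one that the wording permits, not one that the trial is bound to commit. A reader might infer that the primary analysis will have double the nominal error rate. The article does not support that, because it neither selects EM nor says that condition enters the imputation model.

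Second, the planned run without drop-outs is a real safeguard. A reader might infer that it would miss the problem; it would not. In the same scenario at ρ = .5 (8,000 runs, null true), EM with condition rejects in .098, completers in .050, and both in .050. Nearly all of the excess therefore appears as disagreement between the two planned analyses. Where condition is left out, completers recover about .57 while EM gives .456. What does not stand is that this settles the matter: the article does not say which result governs when the two disagree. Nor does disagreement alone show whether false precision, dilution or informative drop-out is the cause.

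Third, the variables in the imputation model, the pooling rules and any missing-not-at-random analysis are details that an article may leave to the analysis plan. This is fair, and their absence is not the point here. The point is the pairing of EM with MI as equals, which is stated in the text.

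**Conclusion.** The point holds in conditional form. The article allows a single EM-completed data set to be analysed by RM ANOVA as if this were equivalent to MI. At 20% missing and 63 per arm, the consequence is a type I error of about .09 to .11 if condition is in the EM model or EM is run by arm, or an unchanged type I error with about 20% dilution if it is not.

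The size rests on an assumed correlation of .2 to .7, on the whole 20% being missing at post-test, and on normal outcomes. With less drop-out the inflation is smaller. For depressive symptoms over five time points the inflation is of similar size or somewhat larger. The choice of method should be fixed before unblinding.

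**What to change.** Strike EM from the sentence on missing values and name one primary method:

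- MI with condition, baseline and all time points in the imputation model, combined by Rubin's rules; or
- a likelihood-based linear mixed model on all observed data, moved from a possibility to the stated primary analysis.

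Keep the analysis with and without drop-outs, and state that the named primary analysis governs if the two differ. A delta-adjusted missing-not-at-random analysis may be added as an optional extra; it should not replace the include/exclude check.

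The cost is a change of wording, a little more analysis work and slightly wider intervals than EM would give. Sample size, visits and measures are unaffected. In the simulations MI kept power at .82 for the planning effect, so the planned 126 remain sufficient under the plan's own assumptions.

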#### Randomization and blinding

Participants are randomly allocated to one of the two groups, right before the first training session. Randomization is computerized and stratified for depression severity (<39 = moderate; 39–48 = severe; > 48 = very severe) at baseline, as assessed by the Inventory of Depressive Symptomatology self-report (IDS-SR; [52]), as well as for age (18–35 years; 36–50 years; 51–65 years). In case participants indicate, that they want to discontinue with the study and withdraw consent for using their data, intervention allocation is corrected for the excluded participants.

Based on the IDS-SR score and age, the computer generates a random 5-digit number, which is linked to one of the two training conditions and which further identifies participants and their documents. This blinding code is managed by an independent statistician and revealed to researchers only, after all participants have completed the last assessment. Hence, both participants and researchers are blind to the training conditions.

To assess if participants remained blinded to their group allocation, all participants fill in an awareness check at post-test, investigating which training condition (PT or ST) they believe they have been enrolled to.

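### Attentional bias and IDS-SR are tested by an unadjusted change-score analysis that omits the stratification factors and adjusts for baseline only if imbalance is seen; prespecified baseline adjustment would be more precise

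*Protocol article*

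**What the plan says.** All from the protocol article.

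- **Randomization and blinding:** "Randomization is computerized and stratified for depression severity" at baseline in three IDS-SR bands, "as well as for age (18–35 years; 36–50 years; 51–65 years".
- **Clinical evaluation, main model:** effects on IDS-SR and attentional bias "will be tested by means of RM ANOVAs, with condition (PT, ST) as between-subjects factor and time (pre-test, post-test) as within-subjects factor". No stratum or age term is named.
- **Clinical evaluation, long-term effects on depressive symptoms:** "the analysis of this primary outcome parameter will be repeated over five time points", with baseline as one of the five.
- **Clinical evaluation, covariates:** "All analyses will be conducted with and without covariates, in case variables are unevenly distributed across groups", for the stated purpose of testing robustness. The examples are "bias or depression at baseline, number of previous depressive episodes, or number of completed training sessions". Age is not among them.
- **Clinical evaluation, alternative model:** "more recent statistical developments including linear mixed models (LMM) might be considered when analyzing the data". Its covariates are not described.
- **Sample size:** the authors "conservatively assume a small to medium effect size of" η² = .02 (f = .142). They use a repeated-measures within-between interaction over two time points with α = .05 and power .80. This gives 100 evaluable participants, or 126 after 20 % attrition. No pre-post correlation is given.

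**The concern.** In a randomised trial the arms have the same expected baseline, so a change-score analysis and an ANCOVA on the post-test value estimate the same effect. The change score subtracts the whole baseline value, whatever the correlation. ANCOVA subtracts only the part that predicts the outcome, so it is more precise whenever ρ is below 1. The article expects small effects, so precision matters.

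Three features of the plan work against precision and clarity:

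- The main model leaves out the variables on which randomisation is stratified. Where a stratifier predicts the analysed quantity, the unadjusted standard error does not credit the balance that stratification achieved. Baseline IDS-SR does predict IDS-SR change when ρ is below 1.
- Baseline adjustment depends on observed imbalance. The gain in precision does not come from correcting imbalance and should not wait for it.
- The number of completed sessions is a post-randomisation variable that the assigned training may influence. Conditioning on it can bias the comparison of randomised groups.

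**Working it through.** **Inputs.** From Sample size: f = .142, N = 100 evaluable (50 per arm), α = .05, two time points. Assumed, because the article does not give it: ρ. I use .5, with .2 and .7 as a range. A low ρ is plausible for a reaction-time difference score, but that too is an assumption.

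**Step 1: reproduce the plan's figure.** For the condition × time interaction, λ = f²·N·2/(1−ρ) with 1 and N−2 degrees of freedom. At ρ = .5, λ = .142² × 100 × 2/.5 = 8.07, and power with 1 and 98 df is .803. The smallest even N reaching .80 is 100, as stated. Then 50/0.80 = 62.5, so 63 per arm and 126 in total. A version without the correlation term (λ = f²·N) needs N = 392 and does not reproduce 100, so I do not use it.

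**Step 2: variance ratio.** With equal variance σ² at both time points:

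- change score: 2(1−ρ)σ²
- ANCOVA residual: (1−ρ²)σ² = (1−ρ)(1+ρ)σ²
- ratio: (1+ρ)/2, which is below 1 for every ρ below 1.

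**Step 3: power at N = 100 and f = .142.** Divide λ by the ratio and use 1 and 97 df.

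| ρ | λ, RM ANOVA | power | ratio | λ, ANCOVA | power | N for .80: RM ANOVA → ANCOVA |
|---|---|---|---|---|---|---|
| .2 | 5.04 | .60 | .60 | 8.40 | .82 | 158 → 96 |
| .5 | 8.07 | .80 | .75 | 10.75 | .90 | 100 → 76 |
| .7 | 13.44 | .95 | .85 | 15.82 | .98 | 62 → 52 |

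**Step 4: cost of extra terms.** This was simulated at N = 100 with 6,000 runs per ρ. The effect was scaled so that the change-score test has about .80 power. Four categorical severity and age terms with no prognostic value beyond baseline were added to the ANCOVA. Power fell as follows:

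- ρ = .2: 94.9 % to 94.3 %
- ρ = .5: 89.8 % to 88.7 %
- ρ = .8: 84.8 % to 82.5 %
- ρ = .95: 80.8 % to 79.4 %, against 80.1 % for the change score.

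**Step 5: omitted strata, IDS-SR only.** This was simulated under no effect at N = 100, assuming three severity strata of about equal size with balanced allocation inside each. The change-score test at nominal 5 % rejects in about 2 % (ρ = .2), 3 % (ρ = .5) and 4 % (ρ = .7) of runs, while ANCOVA stays near 5 %. Under stratification, then, part of the loss appears as an overstated standard error.

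**The case against.** - **The plan does not ignore baseline.** A reader might infer that it does. It provides covariate-adjusted runs and names baseline bias and baseline depression, the latter being the score from which the severity stratum is cut. With two time points, adding baseline as covariate to the change analysis is algebraically the ANCOVA. This objection stands. The weakness is that the better analysis is conditional and secondary. Only age goes unmentioned, and the list is given as examples.
- **The plan does not leave a free choice between two p-values.** The unadjusted RM ANOVA comes first and the covariate runs test robustness, so the natural reading is unadjusted main, adjusted sensitivity. This stands.
- **Adjustment is not free.** Step 4 shows a cost of 0.6 to 2.3 points for four uninformative terms, which at ρ = .95 cancels the gain. The article has no evidence that age predicts either outcome or that severity predicts attentional bias. This stands, and it argues for continuous covariates.
- **The gain is not fixed.** Holding unadjusted power at .80 for every ρ would suggest a rise to .95 at ρ = .2 or .86 at ρ = .7. Under the article's own f those pairs do not describe this design; the table in Step 3 does.
- **RM ANOVA is valid in a randomised trial and matches the sample-size method.** True; the point concerns efficiency and prespecification.
- **Covariate lists are often left to an analysis plan.** True, but the article itself fixes the model, the trigger and an unsuitable example covariate.

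**Conclusion.** The point holds as an inexpensive improvement for attentional bias and IDS-SR. The main analysis is an unadjusted change-score test that leaves out the stratification factors, and baseline adjustment waits on observed imbalance. At ρ = .5, prespecified baseline adjustment cuts the variance by 25 % and raises power from about .80 to .90. The gain in power is larger at low ρ and small at high ρ. These figures assume equal variances at both time points, 100 evaluable participants, f = .142 and an unstated ρ.

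A reader might go further and conclude that the trial is underpowered. This point does not show that: the stated N reproduces at 80 % power with ρ = .5. Nor does it make the planned test biased. It does not extend unchanged to the third primary outcome. The speech task takes place only at post-test, so its rating before stress is itself taken after randomisation.

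**What to change.** For attentional bias and IDS-SR at post-test, prespecify as primary an ANCOVA of the post-test value on condition. Always include the continuous baseline value of the outcome, baseline IDS-SR and age. For IDS-SR as outcome, the first two are the same term.

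For the five-time-point analysis, use a mixed model with the four post-baseline values as outcomes and the same covariates. Baseline cannot simply be added to the quoted model, where it is already a level of the outcome.

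Keep the unadjusted RM ANOVA as the sensitivity analysis. Delete the imbalance trigger, and remove the number of completed sessions from the covariates for the intention-to-treat comparison. For the speech task, state that no pre-randomisation value of the outcome exists.

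The cost is a change of wording and two or three model terms. All variables are already collected. The loss if the terms are uninformative is smaller with continuous IDS-SR and age than the roughly 2 points at most seen with four categorical terms.
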